**Methods/design:**

Physician participants will be randomly assigned in groups (*n* = 3/group) to a 30-h CST program (experimental group) or to a waiting list (control group). The training program will include learner-centered, skills-focused, practice-oriented techniques. Training efficacy is assessed in the context of an encounter with a simulated advanced stage cancer patient at baseline and after the CST for the experimental group, and after four months for the waiting-list group. Efficacy assessments will include communicational, psychological and physiological measures. Group-by-time effects will be analyzed using a generalized estimating equation (GEE). A power analysis indicated that a sample size of 60 (30 experimental and 30 control) participants will be sufficient to detect effects.

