### Study design

Participating physicians will be randomly assigned to either the experimental group or the control group (Fig. 1). After baseline assessment, participants in the experimental group will attend a 4-month training program followed by a post assessment. Participants in the control group will be placed on a waiting list after baseline assessment and will be reassessed four months later. The process of randomization after baseline will allow for a double-blind assessment at baseline.

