#### CST logistics

The CST is a manualized program comprised of ten 3-h sessions (30 h) spread over four to five months. Each training group will include three physicians. The training will be conducted at locations and times choosen by the physicians within each group. The trainer of the experimental group will be an experienced facilitator who will conduct all training sessions ([name]). The training timetable will not include more than two 3-h sessions in one day. Physicians will have the opportunity to register in groups of three or individually. In the latter case, physicians will be assigned to groups according to geographical proximity.

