#### Statistical analyses

The primary outcome of the current study is the physicians’ increased communication performance after training during this encounter. A power analysis has been performed, based on a previous longitudinal study assessing physicians’ communication performance composite score in an encounter with a simulated advanced-stage cancer patient (Mean = 26; SD = 8) [54]. This power analysis was conducted considering 4 independent conditions according to the time (time 1 *versus* time 2) and the group (experimental *versus* control group). As there is no previous study assessing the efficacy of an intensive communication skills training program on physicians’ communication about uncertainty and hope, it was hypothesized that physicians in the control group will maintain a stable performance score from time 1 to time 2. It was also hypothesized that physicians in the experimental group will improve their performance score by 20% from time 1 to time 2. Sample size calculation has been based on an 80% power, a one-sided α = 0.05 t-test and an effect size of 0.65. Considering this power analysis, 60 evaluable physicians are therefore needed for the efficacy assessment. Considering a drop-out rate of 20%, 12 physicians should be moreover recruited (72 physicians in total). It should be recalled at this level that one trainer only will conduct the training of the experimental group. Secondary, to assess also the CST program efficacy, group-by-time effects will be performed using generalized estimating equation (GEE) on psychological, physiological and communicational assessments performed during the encounter with the simulated patient.

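### Unless it is corrected for small samples and clustered on the training trio, the named GEE would exceed its 5% level with about 20 trios

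*Protocol article*

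**What the plan says.** GEE is the only efficacy model that the article names. The abstract gives it no rank: "Group-by-time effects will be analyzed using a generalized estimating equation (GEE". The Statistical analyses section introduces it with "Secondary, to assess also the CST program efficacy" and says that "group-by-time effects will be performed using generalized estimating equation (GEE", applying it to the communication, psychological and physiological measures alike. The same section sizes the trial with a one-sided 5% t-test at an effect size of 0.65, treats the four group-by-time cells as independent, asks for 60 evaluable physicians and recruits 72 to allow for 20% drop-out.

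On the unit of assignment, the abstract says "Physician participants will be randomly assigned in groups (*n* = 3/group", while the Study design section says "Participating physicians will be randomly assigned to either the experimental group or the control group" and does not mention trios. On delivery, CST logistics says "Each training group will include three physicians". Physicians may register as a ready-made trio or individually, in which case they are grouped by geographical proximity.

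The article does not state the GEE's cluster unit, working correlation, variance estimator, reference distribution or treatment of missing scores.

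**The concern.** Two features of the design strain an ordinary GEE.

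- **Few clusters.** The sandwich variance is biased downward when there are few independent units, and a normal reference makes matters worse. If trios are assigned, the independent units are trios, about ten per arm. Clustering on physician instead gives more units but treats three people taught together, and perhaps already colleagues, as unrelated.
- **Drop-out.** One arm must attend ten 3-hour sessions and the other waits, so loss could plausibly depend on baseline performance differently in the two arms. GEE does not, in general, guarantee an unbiased estimate in that case.

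At stake are the p-values and confidence intervals for every outcome analysed this way and, under particular conditions, the group-by-time estimate itself.

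**Working it through.** **Inputs from the article.** Mean 26, SD 8, improvement 20%, one-sided α 0.05, power 80%, 30 + 30 evaluable, 72 recruited, trios. **Assumed, because the article gives neither:** trio ICC (0 to 0.2, on the analysed change score) and the correlation between visits (0.3 to 0.7).

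**1. The plan's own figure.** 0.20 × 26 = 5.2, and 5.2 / 8 = 0.65. A one-sided two-sample t-test at 30 per arm has power 0.800, so 60 is reproduced.

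**2. Number of clusters.** 60 / 3 = 20 trios, K = 10 per arm. 72 / 3 = 24 trios, K = 12 per arm.

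**3. Size of the uncorrected test.** In a balanced model with group, time and group-by-time, the ordinary sandwich standard error (SE) is √((K−1)/K) times the unbiased one. The statistic that is compared with z really follows a t distribution with 2K−2 df after rescaling, so two-sided size = P(|t(2K−2)| > 1.96 × √((K−1)/K)); one-sided, 1.645 replaces 1.96.

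| Cluster | K per arm | SE factor | Two-sided | One-sided |
|---|---|---|---|---|
| Trio, 60 evaluable | 10 | √0.9 = 0.949 | 7.9% | 6.8% |
| Trio, all 72 | 12 | 0.957 | 7.4% | 6.5% |
| Physician, 60 evaluable, ICC 0 | 30 | 0.983 | 5.9% | 5.6% |

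**4. Clustering on physician when trios correlate.** With three per trio the true variance is 1 + 2 × ICC times the assumed one: 1.1, 1.2 and 1.4 at ICC 0.05, 0.1 and 0.2. Simulated two-sided size (40,000 trials per setting, 20 trios):

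| ICC | Both arms | Trained arm only |
|---|---|---|
| 0.05 | 7.2% | 6.6% |
| 0.1 | 8.6% | 7.0% |
| 0.2 | 11.4% | 8.3% |

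**5. Corrected test.** In the balanced case the Kauermann-Carroll correction multiplies the variance by K/(K−1), which removes the bias. With t on 18 df this is a t-test on trio mean changes; its simulated two-sided size was 4.8-5.1% across all these ICCs. Mancl-DeRouen multiplies by (K/(K−1))², leaving the SE √(10/9) = 1.054 times too large. Its two-sided size is P(|t(18)| > 2.101 × 1.054) = 4.0%, slightly conservative.

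**6. Power, one-sided, effect size 0.65.** At ICC 0 with 20 trios, the uncorrected physician-level z-test has 0.81 and the corrected trio-level test 0.78. The corrected test has 0.75, 0.71 and 0.65 at ICC 0.05, 0.1 and 0.2 in both arms; with 24 trios it has 0.85, 0.81, 0.79 and 0.73 at ICC 0, 0.05, 0.1 and 0.2. The decline with ICC is the price of clustering itself, not of the correction.

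**7. Drop-out.** Simulation with 36 per arm, about 20% loss, true effect 5.2, log odds of loss changing by 1 per SD of baseline, no trio effect, 250 trials per setting (Monte Carlo SE 0.10-0.16). Working independence compares completers' follow-up scores with everyone's baseline, so each arm shifts by visit correlation × 8 × the mean baseline of completers in SD units. The shifts cancel when both arms lose the same kind of physician.

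| Loss depends on baseline | Independence GEE | Exchangeable GEE |
|---|---|---|
| Same way in both arms | 5.1-5.4 | 5.1-5.4 |
| Trained arm only | 5.5-6.4 | 5.0-5.4 |
| Opposite ways | 6.0-7.3 | 5.1-5.3 |

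Exchangeable GEE and a linear mixed model differed by at most about 0.07 points.

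**The case against.** The strongest reply is that the article does not specify the analysis being criticised. It is a condensed account, and cluster unit, working correlation and small-sample correction are details that an analysis plan may settle. That stands, and it rules out four stronger readings that a reader might infer.

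- **That the trial's standard errors are too small.** The article does not say that an uncorrected sandwich will be used. What can be said is that both ordinary implementations miss the level unless corrected.
- **That 20% drop-out biases the GEE because it needs missingness completely at random.** With two visits and a continuous outcome, material bias needs working independence together with drop-out that depends on baseline differently by arm. Nothing in the article shows either.
- **That GEE must give way to a mixed model.** A corrected GEE does the same job for the standard errors, and some coded communication measures may be counts, for which a linear mixed model is not clearly better. A mixed model with only a time-constant trio intercept can fail too: it does not represent similarity that arises through training. In a simulation of such a model (1,500 runs, visit correlation 0.5, t reference with 18 to 57 df in place of Kenward-Roger), a trio effect at follow-up only, in both arms, gave two-sided size 7.0-8.5% at ICC 0.1 and 9.9-11.6% at ICC 0.2.
- **That the primary test is affected.** The statistics section ranks the GEE as secondary and ties the sizing to a t-test; the abstract names GEE without rank. The article does not settle it.

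The objection does not remove the point that the method is named, the trios are stated, and leaving the cluster unit open rescues neither default.

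**Conclusion.** The concern holds in conditional form. With about 20 evaluable trios, a GEE without small-sample correction is anti-conservative: about 7.9% two-sided and 6.8% one-sided if clustered on trio, and 5.9% two-sided if clustered on physician with no trio correlation, rising to about 7-11% when an ICC of 0.05-0.2 in both arms is ignored. The trio-level figures rest on a balanced layout and a normal outcome; the range for physician clustering also rests on assumed ICCs. If only trained physicians form trios, as the Study design wording would allow, the range is about 6.6-8.3%.

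The drop-out issue is narrower. It is a reason not to use working independence for the pre/post pair, not a reason to abandon GEE. An exchangeable correlation does not protect against loss that depends on the unseen follow-up score; nor does a mixed model.

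The inflation is moderate and cheap to prevent, so the plan should be changed. How far it touches the main conclusion depends on which analysis is declared primary.

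**What to change.** Keep GEE and specify it:

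- name the trio as the cluster, and reconcile the abstract and Study design on whether trios or physicians are assigned, because this defines the clusters in the waiting-list arm;
- use a bias-corrected sandwich (Kauermann-Carroll or Mancl-DeRouen) with a t reference on trios minus 2 df, which is 18 with 20 trios and 22 with 24;
- do not use working independence for the pre/post pair;
- state whether this GEE or the t-test is the primary analysis.

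For continuous outcomes, a REML mixed model with small-sample degrees of freedom is an equivalent choice, provided that its trio effect may differ between baseline and follow-up (a trio-by-time term, not only a constant trio intercept).

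The cost is wording in the analysis plan, a little programming and slightly wider intervals: one-sided power about 0.78 instead of 0.81 at trio ICC 0 with 20 trios, and a little less with Mancl-DeRouen. Neither conduct nor sample size has to change for this correction.

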## Discussion

Due to medical progress, cancer is now recognized as a long-term chronic disease necessitating optimal communication between physicians and their patients to help patients cope with uncertainty and to promote hope regarding the future. However, due to a lack of specific training in medical curriculum [20], physicians frequently experience difficulties in communicating these issues with cancer patients.

The current paper describes a randomized controlled trial protocol assessing the efficacy of a CST program aimed at improving physician ability to communicate about uncertainty and hope in encounters with cancer patients. The CST program includes learner-centered, skills-focused, practice-oriented techniques with small groups of physicians (n = 3/group). The CST efficacy will be assessed at the communicational, psychological and physiological levels. Results from the study will provide information regarding CST techniques and content that will be beneficial in the development of programs to improve physician communication skills about uncertainty and hope with cancer patients.

The development of such CST programs will lead to positive outcomes for healthcare professionals, cancer patients and their relatives. Improving physician ability to communicate about uncertainty and hope with cancer patients may increase work satisfaction [30], decrease risk of staff burnout [25], improve cancer care delivery [32], limit risk of increased costs [25], limit use of healthcare services [31] and reduce healthcare professional decisional conflict and regret [8, 10–14]. Moreover, improving communication between physicians and patients about uncertainty and hope may increase patient satisfaction with healthcare and fulfill patient desire for information and maintenance of hope [6, 9, 34]. In addition, effective communication may improve patient adjustment to cancer [1, 7, 17], quality of life, maintenance of a positive outlook on future treatments and decrease decisional conflict and regret [1, 18]. Future studies should further assess the usefulness of the CST program used in the current study on all these outcomes.

## Abbreviations

CPO: Centre de Psycho-Oncologie
CST: Communication skills training
GEE: Generalized estimating equation
